### Study Objectives

This study is part of the Innovative Medicines Initiative (IMI) Patient Preferences in Benefit-Risk Assessments during the Medical Product Lifecycle (PREFER) project (21). This 5-year research project will develop evidence-based recommendations to guide industry, regulatory authorities, and health technology assessment bodies on when and how PP on benefits and harms should be assessed and used to inform decision making throughout the medical product life cycle (for a brief overview, see https://www.imi-prefer.eu/ or https://www.imi.europa.eu/projects-results/project-factsheets/prefer).

This study has both clinical and methodological endpoints. The clinical endpoints of this study are:

What are the MAR and MAB that patients would accept for treatment alternatives?What are the clinical, demographic and psychological variables that may explain patients' preferences? In particular, we will explore to what extent PPs vary with disease stage and line of treatment, age, gender, educational level, and psychological characteristics of the patients (i.e., health literacy and health locus of control).

As methodological endpoints, the study will assess the following:

How similar are the results acquired from the two different methods (i.e., DCE and SW) applying the same set of attributes on the same population? To what extent assessing preferences for treatment alternatives in NSCLC patients with a DCE will provide comparable information if compared to a different method like the SW? The aim is to highlight the strengths and weaknesses of two different methodologies in identifying and profiling different treatments within the context of patient management.Would an educational tool be perceived as being a useful way to provide information on treatment attributes and attribute levels, and to teach participants how to perform different choice tasks?

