### Statistical Analyses

The clinical objective of this study is to assess patients' preferences for relevant treatment attributes related to LC treatment alternatives. To determine preferences of study participants, attribute (level) estimates and the conditional relative importance of attributes will be explored in the DCE using conditional logit models. For the final analyses, preferences for attributes of NSCLC treatment random parameters logit (RPL) modeling and latent class analysis (LCA) will be considered. Final decisions on the modeling procedure will be made once data collection has been completed and explored. This decision will be based on model fit and clinical interpretation. Different models might be used to answer the different research questions in this case study. Heterogeneity of preferences and the impact of participant characteristics among which psychological variables will be investigated *via* LCA or subgroup analyses using RPL.

For the SW, each attribute is first ranked by the participants, and then the relative importance is indicated through point allocation. The rank order will be turned into weights using a rank-to-weight method, rank order centroid method (35). Using this approach, the average weight per attribute over the entire group of respondents is then calculated and it becomes possible to statistically investigate whether weights differ between subgroups.

The MAR and MAB values for benefits and risks of interest will be determined based on DCE outcomes.

The methodological objective of this study is to evaluate the similarity of DCE and SW in assessing preferences for treatment alternatives in NSCLC. The results of the DCE and SW will be compared qualitatively and quantitatively to evaluate whether the results are different when applying two different methods. As a first step, validity checks, completion time (through log information), dropout, and response to feedback questions will be compared between the two methods. Second, the relative importance of the included attributes will be compared between the two methods.

PP heterogeneity and the influence of participants' clinical (i.e., disease stage and line of treatment), socio-demographic (i.e., age, gender, and educational level), and psychological characteristics (i.e., health literacy and health locus of control) will be investigated by applying appropriate statistical models including LCA and/or subgroup analyses.

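### The objective is how similar DCE and SW results are, but the analysis is framed as a search for differences and describes no within-person comparison, although the data are paired

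*Protocol article*

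**What the plan says.** Study Objectives (protocol article) poses the methodological question as "How similar are the results acquired from the two different methods", with the same attributes and the same population. Statistical Analyses repeats it: "The methodological objective of this study is to evaluate the similarity of DCE and SW in assessing preferences". The next sentence sets the comparison as qualitative and quantitative, "to evaluate whether the results are different when applying two different methods". After validity checks, completion time, dropout and feedback, the preference results are dealt with in one sentence: "Second, the relative importance of the included attributes will be compared between the two methods".

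For SW, "The rank order will be turned into weights using a rank-to-weight method, rank order centroid method"; then "the average weight per attribute over the entire group of respondents is then calculated", after which "it becomes possible to statistically investigate whether weights differ between subgroups". For the DCE, conditional logit is the exploratory model. Random parameters logit (RPL) and latent class analysis are to be considered for the final analyses, and different models may serve different questions.

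Under Design, randomization decides only which task comes first, so every participant is offered both. Handling Missing Data restricts the DCE–SW comparison to respondents who fully completed both.

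**The concern.** Similarity and difference are separate inferential questions. Failing to detect a difference does not show agreement, and detecting one does not show that it matters. Here the objective asks the first question and the next sentence describes the second.

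The design also yields two answers from each person, which is the information needed to see whether the methods tell the same story about a patient. An average over the whole group discards it: two methods can give equal averages while ranking individuals quite differently.

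The Discussion calls this a main methodological endpoint and expects it to inform recommendations on how preference data should be measured. The study is also about preference heterogeneity, where group averages say least.

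**Working it through.** The documents give no standard deviation, significance level, margin or agreement measure for the method comparison, so there is no planned figure to reproduce. The inputs they do give are 510 respondents (Sample Size Estimation), five attributes (Attributes and Levels Development), 12 choice tasks per patient (DCE and SW Task Construction), rank order centroid weights (Statistical Analyses) and completers of both tasks as the comparison set (Handling Missing Data). Everything else below is an assumption.

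**1. Rank order centroid weights.** For rank i of 5, the weight is (1/5) × (1/i + … + 1/5).
- First: (1 + 1/2 + 1/3 + 1/4 + 1/5)/5 = 2.2833/5 = 0.457
- Second: 1.2833/5 = 0.257
- Third: 0.7833/5 = 0.157
- Fourth: 0.45/5 = 0.090
- Fifth: 0.2/5 = 0.040

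These are constants. A patient's weights carry the rank order and nothing else.

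**2. Equal averages with no agreement, by construction.** Suppose half the patients rank A to E and the other half E to A, and that every patient reverses the order between methods. Under both methods the group means are
- A and E: (0.457 + 0.040)/2 = 0.248
- B and D: (0.257 + 0.090)/2 = 0.173
- C: 0.157

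The averages are identical, yet every patient's weights for A and E differ by 0.417 between methods.

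**3. The same point by simulation.** 500 studies of 510 patients were simulated. Both methods shared the group utilities 1.5, 0.8, 0.5, 0.2 and 0, but each patient's two rankings were drawn independently (Gumbel errors). Both sides were expressed as rank order centroid weights, and five unadjusted paired t-tests were run at 5%.
- Largest gap between group mean weights, averaged over studies: 1.3 percentage points.
- Studies with at least one significant attribute: 21.4%, so 79% had none. The true means are equal, so the 21.4% are false positives; five independent tests would give 1 − 0.95^5 = 22.6%.
- Patients with the same top attribute: 27%. This follows directly: the first-choice probabilities are 0.424, 0.210, 0.156, 0.115 and 0.095, and their squares sum to 0.270.
- Patients with the same full ranking: 1.5%. Mean within-attribute correlation: 0.00.

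**4. Small differences, if a paired test were used.** The smallest significant mean difference is 1.96 × SD/√n, where SD is that of the within-person DCE minus SW difference, assumed to be 0.10 to 0.20.
- n = 510: 1.96 × 0.10/22.58 = 0.009 to 1.96 × 0.20/22.58 = 0.017 (0.013 at SD 0.15)
- n = 300, as an assumed lower number of completers: 0.011 to 0.023

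This calculation needs individual DCE importances. It does not describe a comparison of group averages, where the DCE standard error comes from the choice model.

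**5. A caution about comparing weights at all.** Let all patients rank identically under both methods. If the DCE importances are 0.60/0.20/0.10/0.06/0.04, the centroid weights differ from them by −0.143, +0.057, +0.057, +0.030 and 0.000. If they are 0.30/0.25/0.20/0.15/0.10, the gaps are +0.157, +0.007, −0.043, −0.060 and −0.060. Gaps of 14 to 16 points can therefore come from the weighting rule alone.

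**The case against.** The strongest reply is that the text states no faulty decision rule. No test, significance level or p-value is named, a qualitative comparison is foreseen, and speaking of similarity in one sentence and difference in the next may be ordinary language for one comparison. A reader might infer that the plan tests for difference and will therefore err in both directions, declaring trivial gaps and missing real disagreement. The documents do not support that: the trivial-difference risk in step 4 arises only if a significance test on individual differences is used.

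The second reply is that the question concerns the same population, so comparing population-level importances is a legitimate answer. That stands for the population question. It does not settle agreement within patients, on which the plan is silent although the data allow it.

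Third, a reader might infer that the plan compares group averages only. The whole-group average is stated for SW alone. The level of the DCE–SW comparison is left open, and RPL, if chosen, would permit individual estimates. Group level is the natural reading, not an explicit statement.

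Fourth, independent answers within each patient are an extreme case with no support in the documents, and the simulation represents both methods by rank weights, not by a fitted choice model. The 79% and 27% illustrate a mechanism and are not forecasts. All of this stands and limits the point.

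A missing margin or agreement statistic could be left to a fuller protocol or analysis plan, and the point does not rest on that. It rests on two adjacent sentences that set different aims.

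**Conclusion.** The point holds in conditional form. The stated objective is similarity, the analysis is worded as a search for difference, the SW result is defined only as a whole-group average, and no within-person comparison is described despite paired data on all completers of both tasks. If similarity is concluded from group averages, or from the absence of a detected difference, the study cannot say whether patients' own answers agree.

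The size in practice is unknown because it depends on the true within-person correlation. At the extreme of no correlation, and under the assumed utilities, about four in five studies would show nothing significant while about a quarter of patients shared a top attribute. The algebra of step 2 needs no such assumptions.

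A margin on centroid weight differences alone would not be a sound remedy, since step 5 shows that it could declare dissimilarity when every patient's ranking is identical.

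**What to change.** In Statistical Analyses, state the aim of the method comparison as estimating agreement between DCE and SW. Among completers of both tasks:
- Report, for each attribute, the DCE minus SW difference in relative importance with a 95% interval that respects the pairing, for example by bootstrapping respondents and refitting the choice model.
- Add the within-person rank correlation and the share of patients with the same top attribute, using individual DCE importances from an RPL fitted for this purpose. Show beside that share the value expected if the two answers were unrelated (27% in step 3), so that the observed figure can be read.
- State that a non-significant difference will not be taken as similarity.
- Base the similarity conclusion mainly on rank agreement, or repeat the weight comparison with the points that patients allocate in the SW task, scaled to sum to one, instead of relying on centroid weights alone.

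The cost is additional analysis on data already to be collected, including repeated model fitting for the bootstrap. The main downside is that individual DCE estimates rest on 12 choices each and are shrunken toward the group mean. This affects both the rank correlation and the same-top share, and the report must say so.

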### Handling Missing Data

Respondents who choose not to answer certain demographic or treatment history questions will be noted in the summary statistics, and their responses will be included in the DCE; however, if data required to assign an individual to a subgroup are missing, that individual will be excluded from the subgroup analysis (pairwise deletion). Respondents who do not answer at least one DCE question and at least one SW question in the survey, or who always select the same alternative (either treatment A or treatment B) in all of the DCE questions (“flatliners”), will be analyzed separately as a part of the quality assessment evaluation. For comparing DCE to SW, we will include respondents who fully completed both methods, whereas for the separate analyses on the DCE or SW, we will include respondents that completed parts of the methods.

### Dissemination

The findings of this study will be disseminated *via* international peer-reviewed journals and scientific conferences. The study protocol has been registered on Health Preference Study and Technology Registry (ID: #190183-001). A summary of the study results will also be written for the lay audience and made available to participants and relevant patient organizations for distribution on their own channels. Patient organizations will be approached to help to disseminate the study results to their members.

## Discussion

Decisions related to LC treatments based on their characteristics are preference-sensitive decisions. Specifically, available therapeutic options for these patients have different treatment characteristics and likely impact PP and influence subsequent decisions. For instance, patients with NSCLC might be asked to choose between an aggressive therapeutic option with possible detrimental effect on their quality of life and an alternative treatment with less effectiveness but fewer harmful effects on quality of life. Therefore, it is essential to understand PP, which attributes patients perceive as more relevant, and the amount of risk they may be willing to tolerate in exchange for a minimal level of benefit.

This quantitative protocol describes a study aiming to identify patient-relevant LC treatment attributes and to understand which treatment characteristics are most important for advanced LC patients. The present study has several methodological and clinical endpoints. One main methodological endpoint is to ascertain how much the results acquired from the two methods, DCE and SW, would be similar when evaluated on a sample of NSCLC patients. There is no consensus on which is the best method to gather quantitative treatment preference data with multiple options ranging from simple ranking exercises to complex trade-off methods currently employed. Thus, this study aims to evaluate to what extent assessing preferences for treatment alternatives in NSCLC with a more demanding instrument like DCE will provide higher-quality information if compared to a less expensive method like the SW task. This will inform further research on PP and contribute to the elaboration of international recommendations developed by the PREFER initiative on how preference data should be measured and included into the treatment development life cycle.

Another methodological endpoint is the evaluation of whether an educational tool would be perceived as being useful in providing information on treatment attributes and attribute levels, and to teach participants how to perform different choice tasks. Results from this study may inform further research on the application of video in supporting fragile patients during survey completion.

The clinical endpoints evaluate the MAR and MAB that patients would accept for treatment alternatives and what are the clinical, demographic, and psychological variables that may explain heterogeneity in patients' preferences. The understanding of what patients perceive as important treatment attributes and the amount of risk they may be willing to tolerate in exchange for a minimal level of benefit may inform preference-sensitive decision-making. Moreover, in line with the objectives of the PREFER initiative, the assessment of what individual psychological characteristics may explain preference heterogeneity can enrich the knowledge on PP and guide future research. Including patients that are currently in different stages of the NSCLC disease, this study will allow us to consider the stage of their disease as a factor that might potentially explain differences in their preferences that emerge as relevant to their treatment decision-making.

This newly acquired knowledge will be useful to enhance medical decision-making, promote personalized treatment decisions, and propose and deliver tailored treatments for NSCLC. Overall, the results coming from this quantitative study will be especially relevant to better understand PPs for different NSCLC treatment attributes, inform decision-making regarding available NSCLC therapeutic options, and promote patient-centered healthcare in the development, evaluation, and medical treatment of LC.

## Data Availability Statement

The original contributions generated for the study are included in the article/supplementary material, further inquiries can be directed to the corresponding author/s.

## Ethics Statement

The study was approved by the Ethical Committee of the European Institute of Oncology IRCCS (IEO, Milan, Italy; reference R1142/20-IEO 1206) and the Ethische Commissie Onderzoek UZ/KU Leuven (Belgium; reference S64022). Participants signed a consent form before participating.
